### **12.5.3 Handling of missing values/censoring/discontinuations**

The reasons for incomplete data are many and include major protocol deviations, dropout because of study withdrawal or death, non-attendance at clinical visits, missing questionnaire items, uninterpretable images, etc.

The primary efficacy analysis will be conducted on the PPS population, which is based on complete cases.

Secondary efficacy analyses will be conducted on the FAS population. In time-to-event analyses, dropout and major protocol deviations are accounted for by censoring at the time of dropout or protocol deviation. In cross-sectional analyses and analyses of change between 2 timepoints, only complete cases will be included. Cases with a major protocol deviation before the first timepoint in the cross-sectional or change analysis will be excluded. The longitudinal mixed-effect analyses will be based on the observed cases. Data will be censored after a major protocol deviation. The underlying assumption in all analyses is that missing data are missing at random and not related to the primary outcome.

The proportion of missing data at each time point will be computed for the Early Amyloid PET, Late Amyloid PET, and Free Choice arms separately, and stratified for SCD Plus, MCI, and dementia.

### **12.5.4 Supportive analyses**

Heterogeneity with respect to the effect on the primary variable between centres will be evaluated with the Breslow-Day test of homogeneity. If this effect varies across centres, centre-specific effects will be calculated.

## **12.6 Secondary Analyses**

### **12.6.1 Secondary efficacy variables**

In the analyses of the secondary efficacy variables, a cross-sectional difference between arms in a secondary endpoint at T1, T2, T3, or T4 (see Table 1) will be carried out by a chi-squared test if the endpoint is dichotomous, a 2-sided *t*-test if the endpoint is normal, and Mann-Whitney test if the endpoint is categorical or continuous and non-normal. The effect of baseline characteristics such as age, gender, MMSE, etc will be studied by a linear or logistic regression model.

A difference between study arms in the longitudinal change of a secondary endpoint will be tested by means of logistic or linear regression where the first measurement is a covariate (ANCOVA analysis) and the second measurement is the outcome. Differences in longitudinal

trends between arms will also be examined by means of the mixed-effects regression model. The effects of baseline characteristics such as age, gender, MMSE, etc. will be studied by including them in the regression models.

All tests will be 2-sided and the significance level will be set at 5%. Bonferroni corrections for multiple testing will be applied when appropriate. Point estimates will be presented together with 95% Wald confidence intervals. A 95% non-parametric confidence interval will be constructed if the estimate is non-normal.

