#### **Secondary Efficacy Analyses**

- A difference between the Early Amyloid PET arm and Late Amyloid PET arm in the time to communicate an etiologic diagnosis with a confidence  $\geq 90\%$  will be tested by the log-rank test. The cumulative incidence of diagnoses will be estimated with the Kaplan-Meier method.
- A cross-sectional difference between arms in a secondary endpoint at T1, T2, T3, or T4 will be tested with a chi-squared test if the endpoint is dichotomous, a 2-sided *t*-test if the endpoint is normal, and a Mann-Whitney test if the endpoint is categorical or continuous and non-normal. The effect of baseline characteristics such as age, gender, MMSE, etc will be studied by a linear or logistic regression model.
- A difference between study arms in the longitudinal change of a secondary endpoint will be tested by means of logistic or linear regression where the first measurement is a covariate (ANCOVA analysis) and the second measurement is the outcome. Differences in longitudinal trends between arms will also be examined by means of the mixed-effects regression model. The effects of baseline characteristics such as age, gender, MMSE, etc will be studied by including them in the regression models.
- The Free Choice arm will be divided into 3 equal-sized groups, according to the date of randomisation. For the Free Choice arm, a change in the placement of amyloid PET imaging over time in the diagnostic workup will be tested by a log-rank test.
- For participants in the Early Amyloid PET arm who had a second amyloid PET scan, the difference in amyloid load between the first and the second amyloid PET scan, as indicated by quantitative image assessments, will be tested with a paired data *t*-test. Data will be log-transformed if non-normal.
- All tests will be 2-sided, and the significance level will be set at 5%. Bonferroni corrections for multiple testing will be applied when appropriate. Point estimates will be presented, together with 95% Wald confidence intervals. A 95% nonparametric confidence interval will be constructed if the estimate is non-normal.

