### 4.1.1 Utility of amyloid PET imaging in patient diagnosis and management

The value, timing, and appropriateness of amyloid PET imaging in clinical practice need to be established to allow its cost-effective implementation in the diagnosis process [Hornberger et al, 2015] of cognitive decline and dementia. This study (AMYPAD Diagnostic and Patient Management Study 01) will determine in a real-life clinical setting for whom diagnostic amyloid PET imaging is appropriate, when this is best performed, and how the resulting information is influencing diagnostic confidence, patient management, and ultimately decision trees and cost-effectiveness of dementia care.

Specifically, we will study 3 groups of patients presenting to memory clinics with a cognitive impairment due to AD, specifically those with subjective cognitive decline plus (SCD Plus), mild cognitive impairment (MCI), and dementia, to determine when amyloid PET imaging helps to exclude AD aetiology (negative predictive value) or conveys an increased risk of AD

(positive predictive value) vis-à-vis other information and evidence (clinical, structural imaging, genetic, CSF). Ultimately, the AMYPAD Diagnostic and Patient Management Study will deliver an encompassing diagnostic algorithm allowing a cost-efficient implementation of amyloid PET imaging in the clinical practice.

We will study the impact of the information provided by amyloid PET imaging beyond diagnosis by determining the impact on patient management and health resource utilisation, both in the current era of symptomatic treatment and in the context of potentially effective disease-modifying therapies aimed at lowering A $\beta$  in the brain. Furthermore, we will determine if our diagnostic algorithm is cost-effective from a health care perspective through providing the input of economic modelling, in the context of the current regulatory perspective.

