### 4.1.3 AMYPAD Diagnostic and Patient Management Study

To identify the optimal window of opportunity for possible intervention in the A $\beta$  pathway, researchers must establish in detail the sequence of events on the path towards AD.

This study will select and follow up a memory clinic population suspected of possible AD, focusing on those with subjective cognitive decline plus (SCD Plus), mild cognitive impairment (MCI), and dementia, to determine the utility of amyloid PET imaging with regards to change in diagnosis, diagnostic confidence, decision trees, and alterations between planned and actual patient management plans.

Through a European network of diagnostic memory clinics and affiliated PET centres, we will determine:

- Impact on diagnostic thinking and patient management
- Impact on diagnostic confidence and decision making
- Impact on patient reported outcomes
- Clinical utility of amyloid PET imaging in preclinical phases of AD (patients with SCD Plus)
- Costs and cost-effectiveness of early adoption vs late adoption of amyloid PET imaging
- Standardised methods of image quantitation across the PET tracers in order to perform pooled analysis across the AMYPAD program

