##### 10.1.2.3 Health economics

- The impact on patient-related outcomes (cognition, anxiety, depression, coping skills, and quality of life) at T3 vs T2 vs T0 in each arm

- The difference in the cost of diagnostic workup to the etiologic diagnosis with very high confidence ( $\geq 90\%$ ) in the Early Amyloid PET Imaging arm vs the Late Amyloid PET Imaging arm. (In those centres where the subjects in the Early Amyloid PET Imaging arm receive a diagnostic workup in addition to clinical evaluation before baseline, the relative costs will not be considered if the results of those exams are not known by the managing physician before the managing physician makes the etiologic diagnosis.)
- Differences in the use of medical resources (not limited to diagnostic procedures, tests, visits, and hospitalisations) and programs between Early Amyloid PET and Late Amyloid PET arms.
- The number of patients who withdraw from the study and the reasons for withdrawal.

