### **10.3.14 Patient questionnaire (use of medical resources)**

Data from the patient questionnaire on the use of medical resources will be collected at T0, T1, T2, and T3 and recorded in the eCRF. (T1 does not require a clinic visit.)

In those centres where the participants in the Early Amyloid PET arm receive a diagnostic workup in addition to clinical evaluation before baseline, the relative costs will not be considered if the results of those exams are not known by the managing physician before the managing physician makes the etiologic diagnosis.

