#### **12.6.1.3 Health Economics Objectives**

- The impact on patient-reported outcomes (cognition, anxiety, depression, coping skills, and quality of life) at T3 vs T2 vs T0 in each arm
- The difference in the cost of diagnostic workup to the etiologic diagnosis with very high confidence ( $\geq 90\%$ ) in the Early Amyloid PET arm vs the Late Amyloid PET arm. (In those centres where the participants in the Early Amyloid PET arm receive a diagnostic workup in addition to clinical evaluation before baseline, the relative costs will not be considered if the results of those exams are not known by the managing physician before the managing physician makes the etiologic diagnosis.)
- The difference between arms (Early Amyloid PET vs Late Amyloid PET vs Free Choice) in the use of medical resources (not limited to diagnostic procedures, tests, visits, and hospitalisations) and programs.

- The number of patients who withdrew from the study, and the reasons for withdrawal.

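### The rank-test rule for non-normal secondary endpoints does not compare mean costs, which the cost comparison and the economic modelling need

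*Protocol*

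**What the plan says.** Section 12.6.1 sets one rule for "a cross-sectional difference between arms in a secondary endpoint at T1, T2, T3, or T4": chi-squared for dichotomous endpoints, a t-test for normal ones, and otherwise a "Mann-Whitney test if the endpoint is categorical or continuous and non-normal". The synopsis repeats it under Secondary Efficacy Analyses ("a Mann-Whitney test if the endpoint is categorical or continuous and non-normal").

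Two health-economic endpoints sit among these secondary variables without a method of their own:

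- Workup cost: "The difference in the cost of diagnostic workup to the etiologic diagnosis with very high confidence" (sections 10.1.2.3 and 12.6.1.3).
- Resource use: the difference between arms "in the use of medical resources (not limited to diagnostic procedures, tests, visits, and hospitalisations) and programs" (section 12.6.1.3). Section 10.3.14 gives the timing: "Data from the patient questionnaire on the use of medical resources will be collected at T0, T1, T2, and T3".

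Other secondary variables do get a named test: log-rank for time to communicated diagnosis (12.6.1.1) and a paired t-test for change in amyloid load (12.6.1.4).

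The use of the cost data is set out in the background. Section 4.1.3 lists "Costs and cost-effectiveness of early adoption vs late adoption of amyloid PET imaging" among the things to be determined, and section 4.1.1 says "we will determine if our diagnostic algorithm is cost-effective from a health care perspective through providing the input of economic modelling".

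Section 12.6.1 also promises point estimates with 95% Wald intervals, or non-parametric intervals where the estimate is non-normal. It does not say whether the cost estimate is a mean, a median or a shift.

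**The concern.** Total and incremental cost are functions of arithmetic means: the mean per patient times the number of patients gives the budget, and the difference in means is the numerator of a cost-effectiveness ratio. Mann-Whitney asks whether a patient in one arm tends to rank above a patient in the other. The two questions have the same answer only when the arms' distributions have similar shapes.

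The design gives a reason to expect different shapes for part of follow-up. Early patients are scanned within 4 weeks of baseline. Late patients are scanned at 8 months (±8 weeks), and section 9.6 requires that scan to come after the T2 visit. At T1 and T2, therefore, adherent Early patients have had a scan and Late patients have not. If scans are costed, Early carries a near-constant component that Late lacks. Any offset would have to come from other, more variable items.

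At stake is the cost conclusion. The planned test could report a cost difference that does not exist in the means, or stay silent about one that does. The rule also makes the quantity compared depend on a normality verdict: means if costs are judged normal, ranks if they are not.

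**Working it through.** **Plan's own figures.** The protocol states no power or effect size for cost or resource use, so there is none to reproduce. The evaluable number comes from section 12.7: 300 per arm with 10% withdrawal gives 300 × 0.9 = 270. That number is consistent with the stated primary power. With 270 per arm, proportions centred on 0.5 and a continuity correction, differences of 20, 15 and 10 points give 99.6%, 92.7% and 61.0%, against 99.6%, 93% and 61% stated.

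**Step 1: why equal means need not give equal ranks.** Assumptions: Late cost is lognormal with mean 100 and coefficient of variation (CV) 1.0. Early cost is a fixed scan cost 100*s* plus a lognormal remainder with mean 100(1 − *s*) and the same CV. Both means are 100. A lognormal's median is mean / √(1 + CV²), so:

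- Late median = 100 / √2 = 70.7
- Early median = 100*s* + 70.7(1 − *s*) = 70.7 + 29.3*s*; for *s* = 0.2 this is 76.6

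The typical Early patient ranks higher although the means are the same.

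**Step 2: how often Mann-Whitney then rejects.** Simulation at two-sided 5%, 270 per arm, CV 1.0, equal means. A share *q* of Late patients also carries the scan cost, and the Late remainder has mean 100(1 − *sq*), so the Late mean stays at 100.

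| Late patients whose cost includes a scan | *s* = 10% | 20% | 30% | 50% |
|---|---|---|---|---|
| None (as at T1, T2) | 17% | 48% | 80% | 99% |
| Half | 9% | 15% | 30% | 47% |
| 80% | 6% | 6% | 8% | 8% |
| All | about 5% in each | | | |

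Repeat runs differ by one or two points. With no Late scan, a Welch comparison of means stays near 5%. In that row a CV of 0.7 gives 10 / 25 / 53 / 89%, and a CV of 1.5 gives 33 / 82 / 98 / 100%.

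**Step 3: direction.** Both arms lognormal with mean 2,000, 270 per arm:

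- Early log-SD 0.8, Late 1.0: Mann-Whitney rejects in 61%, all with Early higher.
- Early log-SD 1.0, Late 0.8: it rejects in 61%, all with Early lower.

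Across these equal-mean settings Welch rejects in about 4 to 7%.

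**Step 4: a missed difference.** Take both medians as 1,200, with log-SD 0.7 in Early and 1.0 in Late. A lognormal mean is median × exp(σ²/2), so the means are 1,200 × exp(0.245) ≈ 1,533 and 1,200 × exp(0.5) ≈ 1,978. At 270 per arm Mann-Whitney rejects in 6% and Welch in 80%.

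**The case against.** **The rule may not reach workup cost.** It concerns differences at T1 to T4, whereas workup cost accumulates to a patient-specific event. One can read the cost method as simply left to the separate analysis plan foreseen in section 12.1. This stands in part: the rule reaches workup cost only because no other between-arm test is offered. Resource use, collected at T0 to T3, falls under it plainly. A later plan that compared means there would depart from the protocol and need reporting under section 12.11.

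**Estimates with intervals are already promised.** A mean difference with a bootstrap interval would comply with section 12.6.1. This is a real mitigation. But the estimate is not named, and the named test could contradict such an interval.

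**The large rejection rates need an unscanned Late arm.** This stands. The Late scan falls before T3 at 13 months, and Late patients still undiagnosed when scanned carry its cost as well. The upper figures apply to T1 and T2, or to workup cost if few Late patients are scanned before diagnosis.

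**Stronger readings to avoid.** A reader might infer that Early PET will look dearer. The documents do not support this: they give no cost distribution, do not say where savings would fall, and do not say how a scan is costed when tracer doses are supplied free (section 8.1). Step 3 shows that the sign can reverse. A reader might also infer that the cost-effectiveness result itself will rest on a rank test. Nothing says so: models take estimates, not p-values, and section 12 plans no test of cost-effectiveness.

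**Counts.** For numbers of visits or tests, a rank test is a defensible convention. This is accepted in the fix.

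**Conclusion.** The point holds in limited form. The rule fixed in section 12.6.1 does not fit an endpoint whose purpose is a comparison of costs. It applies directly to costed resource use and by default to workup cost, provided that the costs are judged non-normal.

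The size cannot be fixed from the protocol. Under the stated assumptions (lognormal remainder, CV 1.0, scan 10 to 50% of mean cost, equal means, 270 per arm), false rejection runs from about 17 to 99% before the Late scan. It falls to 9 to 47% if half of Late patients' costs include a scan, and is near nominal, about 5 to 8%, if 80% or more do, for example by T3. Another way of keeping the means equal, or other shapes, would move these figures, and the direction of the error is not determined.

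The endpoints are secondary and the primary analysis is untouched. The change is still worth making, because the cost comparison serves a declared aim of the study and the remedy is one sentence.

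**What to change.** Add to section 12.6.1.3, with a matching exception in section 12.6.1 and the synopsis: *Workup cost and costed resource use are compared between arms as differences in arithmetic means with a bootstrap 95% confidence interval (or a Welch t-test), whatever the shape of the distribution. Mann-Whitney is not used for inference on cost.* Medians may be shown as description, and a rank test may stay as a description for counts of individual resource items.

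This changes wording only and needs no new data or patients. The downside is that intervals for mean cost are wider when costs are very skewed, which reflects the real uncertainty about the mean.

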##### 10.1.2.1 Diagnosis and confidence

- The difference between the Early Amyloid PET arm and Late Amyloid PET arm in the time to communicate to the patient an etiologic diagnosis with very high confidence ( $\geq 90\%$ ).
- The changes in the managing physician's etiologic diagnosis at T3 vs T2 vs T1 in each arm.
- The changes in the managing physician's diagnostic confidence at T3 vs T2 vs T1 vs T0 in the Early Amyloid PET vs Late Amyloid PET arms.
- The managing physician's estimate of the likelihood that the patient's symptoms are due to AD at T3 vs T2 vs T1 vs T0 in the Early Amyloid PET arm vs the Late Amyloid PET arm.
- Changes over calendar time in the placement of amyloid PET imaging in the patient workup for participants in the Free Choice arm.

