#### **12.6.1.1 Diagnosis and Confidence**

- A difference between the Early Amyloid PET arm and the Late Amyloid PET arm in the time to communicate an etiologic diagnosis with a confidence  $\geq 90\%$  will be tested by the log-rank test. The cumulative incidence of diagnoses will be estimated with the Kaplan-Meier method.
- Changes in the managing physician's etiologic diagnosis at T3 vs T2 vs T1 in each arm
- The changes in the managing physician's diagnostic confidence at T3 vs T2 vs T1 vs T0, for participants in the Early Amyloid PET arm vs participants in the Late Amyloid PET arm
- The managing physician's estimate of the likelihood that the patient's symptoms are due to AD at T3 vs T2 vs T1 vs T0 in the Early Amyloid PET arm vs the Late Amyloid PET arm.
- Changes over calendar time in the placement of amyloid PET imaging in the patient workup for participants in the Free Choice arm. The Free Choice arm will be divided into 3 equal-sized groups, according to the date of randomisation. For the Free Choice arm, a change in the placement of amyloid PET imaging over time in the diagnostic workup will be tested by a log-rank test.

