#### **12.6.1.2 Patient Management**

- The difference between arms (Early Amyloid PET arm, the Late Amyloid PET arm, or the Free Choice arm) in the number of patients randomised to disease-modifying drug (DMD) or any other AD clinical trial at T2.
- The difference between the Early Amyloid PET arm and the Late Amyloid PET arm in number of participants with changes in the management plan (changes in or start of a new program or pharmacologic treatment) at T1 vs T2 vs T3.

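### The test rule for secondary endpoints sends all multi-category outcomes to a rank test, which is not valid if a nominal outcome such as etiologic diagnosis is compared between arms

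*Protocol*

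**What the plan says.** Protocol section 12.6.1 sets one rule for "a cross-sectional difference between arms in a secondary endpoint at T1, T2, T3, or T4". It names a "chi-squared test if the endpoint is dichotomous", a two-sided t-test if it is normal, and a "Mann-Whitney test if the endpoint is categorical or continuous and non-normal". The synopsis (Secondary Efficacy Analyses) repeats the rule: "a Mann-Whitney test if the endpoint is categorical or continuous and non-normal". Neither place says whether the categories must be ordered.

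For change over time, section 12.6.1 has a separate rule: logistic or linear regression with the first measurement as covariate, and mixed-effects models.

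Section 10.1.2.1 lists as a secondary endpoint "The changes in the managing physician's etiologic diagnosis at T3 vs T2 vs T1 in each arm", and section 12.6.1.1 repeats it without naming a test. The synopsis adds the change from T0 to T1, also in each arm. Table 1 schedules the etiologic diagnosis at T0 to T4.

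On the arms compared, the medical resource use item in section 12.6.1.3 begins "The difference between arms (Early Amyloid PET vs Late Amyloid PET vs Free Choice". Section 10.1.2.3 and the synopsis (Health Economics) define the same endpoint as Early against Late only.

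**The concern.** Because dichotomous outcomes have their own branch, "categorical" in this rule can only mean three or more categories. A rank test needs those categories to have an order. Etiologic diagnosis has none: section 5.3 gives dementia due to Alzheimer's pathology and dementia due to Lewy body pathology as examples, and neither ranks above the other. To run Mann-Whitney on such a variable, someone must number the categories, and the result follows the numbering. A real difference between arms in the mix of diagnoses could be missed, or a conclusion could change with the coding.

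This outcome is central to the rule. The other secondary variables are mostly 0 to 100% ratings, scale scores, costs, times or yes/no counts, which fall under other branches. Etiologic diagnosis is the clearest variable for which the categorical branch would be used.

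A smaller problem concerns resource use. A single Mann-Whitney test, like the t-test beside it, takes two groups, while section 12.6.1.3 names three arms.

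**Working it through.** The protocol gives no figure for this point, so there is none to reproduce. The check asks whether the named test gives one answer on a nominal outcome.

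**Inputs.** 270 per arm is 300 less the 10% withdrawal assumed in section 12.7: 300 × 0.9 = 270. The category counts are assumptions made for illustration; the protocol gives no expected distribution of diagnoses. Take three unordered categories A, B and C.

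| Arm | A | B | C | Total |
|---|---|---|---|---|
| 1 | 120 | 75 | 75 | 270 |
| 2 | 120 | 45 | 105 | 270 |
| Both | 240 | 120 | 180 | 540 |

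**Chi-squared**, sum of (observed − expected)²/expected. The expected counts per arm are half the column totals: 120, 60 and 90.

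- A contributes 0.
- B contributes 2 × 15²/60 = 7.5.
- C contributes 2 × 15²/90 = 5.0.
- The total is 12.5 on 2 degrees of freedom, p = 0.0019. Reordering the columns changes nothing.

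**Mann-Whitney.** U is the number of pairs in which the arm 1 patient has the higher code, plus half the tied pairs.

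- Mean of U under no difference: 270 × 270/2 = 36,450.
- Tie-corrected variance: (270 × 270/12) × [541 − Σ(t³ − t)/(540 × 539)], with t = 240, 120, 180. This is 6,075 × (541 − 73.47), so the SD is about 1,685.
- Tied pairs: 120 × 120 + 75 × 45 + 75 × 105 = 25,650, half of which is 12,825.

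| Coding | U for arm 1 | z | p |
|---|---|---|---|
| A < B < C | 75 × 120 + 75 × (120 + 45) + 12,825 = 34,200 | −2,250/1,685 = −1.34 | 0.18 |
| B < A < C | 120 × 45 + 75 × (45 + 120) + 12,825 = 30,600 | −5,850/1,685 = −3.47 | 0.0005 |

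Of the six possible codings, four give p = 0.18 and two (those with A in the middle) give p = 0.0005. The data are the same in every case.

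**A second hypothetical table**, four categories, 135/45/45/45 against 135/75/30/30. Chi-squared gives p = 0.004. Over the 24 codings, Mann-Whitney p runs from 0.0003 to 1.0, and 8 of the 24 fall below 0.05.

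**Three arms, resource use.** Three pairwise Mann-Whitney tests were simulated under no difference (270 per arm, 4,000 runs, skewed data). The chance of at least one false positive was about 12% with each test at 0.05, and about 4% with each at 0.05/3. Bonferroni-corrected pairwise tests therefore control the error; a single Mann-Whitney test cannot answer the three-arm question.

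**The case against.** The strongest reply is that no listed endpoint requires the faulty comparison. The rule governs cross-sectional differences between arms, and etiologic diagnosis is listed as "Changes in the managing physician's etiologic diagnosis at T3 vs T2 vs T1 in each arm". If change were scored yes or no and compared between arms, it would be dichotomous and go to chi-squared. This stands, and it sets the limit of the point. It does not remove it. Section 5.4.2.1 aims to assess the impact of imaging on changes in etiologic diagnosis, which in a randomised trial invites a between-arm comparison, and the rule exempts no secondary endpoint. The longitudinal rule offers no alternative for unordered categories, since it names logistic and linear regression but no multinomial model. The protocol does not say that diagnosis will be recoded as changed or unchanged.

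A reader might infer that other endpoints are caught as well. The documents do not support that. The management-plan endpoint counts participants with changes, so it is dichotomous. Reasons for withdrawal are listed with no comparison between arms.

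A reader might also infer that the rule cannot compare three arms at all. Trial enrolment is worded as "The difference between arms (Early Amyloid PET arm, the Late Amyloid PET arm, or the Free Choice arm) in the number of patients" randomised to a trial. It is yes/no per patient, so chi-squared applies and handles three arms. Only resource use is touched, and there section 12.6.1 allows Bonferroni correction where appropriate, so corrected pairwise tests are a valid route.

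Finally, section 12.1 leaves further detail to a statistical analysis plan. That would answer an omission, but here the protocol names a test. Section 12.11 requires deviations from the analysis in the protocol to be described and justified in the study report, so a later switch to the suitable test may itself have to be reported as one.

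**Conclusion.** The rule is wrong as written for unordered categories and should be corrected. Its effect is confined to between-arm secondary comparisons of diagnosis categories, if these are made. The primary chi-squared test, the sample size, the log-rank analyses and the dichotomous and two-arm score-based secondary comparisons are unaffected.

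The illustrated size (p = 0.002 by chi-squared against 0.18 or 0.0005 by Mann-Whitney) rests on invented counts. It shows that the result depends on coding; it does not predict what this trial would find. On resource use, the documents contradict each other on which arms are compared. That needs reconciling, but it does not make a three-arm comparison impossible.

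**What to change.** In section 12.6.1 and in the synopsis, replace the categorical branch with one sentence: nominal endpoints are compared with an r x c chi-squared or exact test, and Mann-Whitney is used only for ordinal or non-normal continuous endpoints in two-arm contrasts.

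For medical resource use, make section 12.6.1.3 agree with section 10.1.2.3 and the synopsis on the arms compared. If three arms are kept and the variable is non-normal, name Kruskal-Wallis or Bonferroni-corrected pairwise Mann-Whitney tests.

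The cost is a sentence in two places and one aligned endpoint definition. No data collection, sample size or primary analysis changes.
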